#### Intervention stages

Table 3 describes the stages for the cooking intervention as well as the procedures for the intervention and control groups.

**Table 3 Tab3:** Evaluation measures for university students participating in the Nutrition and Culinary in the Kitchen program

Meeting	Evaluation measures	Intervention group	Control group
1	Online survey at baseline (T1)	Cooking class 1	E-mail contact with a link to the online survey
2	No data collection	Cooking class 2	No intervention
3		Selection and purchase Workshop	
4		Cooking class 3	
5		Cooking class 4	
6	Online survey to be completed right after intervention (T2)	Cooking class 5	E-mail contact with a link to the online survey
7	Follow-up: online survey to be completed six months after intervention (T3)	E-mail contact to answer the survey online	E-mail contact with a link to the online survey
8	–	–	E-mail contact with an invitation to participate in the intervention program

Nutrition undergraduate and graduate students were invited to participate in the facilitators’ group to help during the hands-on cooking classes. They received a theoretical-practical training of 3.5 h that included an explanation on the presentation of each hands-on cooking class, as well as a guided tour to the lab kitchen where the classes would take place. In each hands-on cooking class, there were from four to five facilitators and a coordinating teacher for each group of 10 to 12 students. The coordinating teacher had an undergraduate degree in Nutrition and practical experience in culinary. Though there are a large number of facilitators to assist in the hands-on cooking classes, given guidance from SCT this level of guidance (social support) was considered to be important. Guidance from facilitators encouraged participants culinary skills efforts and contributed through guided practice to attempt to enhance self-efficacy [60].

A pilot study of the first hands-on cooking class was carried out with a group of ten students who were enrolled in their first year of an undergraduate course of the same university to identify any possible adjustments in the presentation of the classes, as well as in the educational material to be used. Materials were adapted from the CWC program and included the following topics that were developed to each cooking class: i) an overview of the cooking class, including its objectives; ii) class agenda, with suggestions on the distribution of time for each activity; iii) instructions about the organization of material and participants for the cooking classes; iv) conceptual issues about nutrition and cooking in relation to the class theme; v) complete recipes as demonstrated by the coordinating teacher and prepared by the participants; and vi) issues for discussion, reflection and challenges subsequent classes (“Seasoning ideas” moment).

### Outcomes measures

#### Primary outcomes

i) accessibility and availability of fruits and vegetables; ii) cooking attitudes; iii) cooking behaviors at home; iv) cooking behaviors away from home; v) produce consumption self-efficacy; vi) self-efficacy for using basic cooking techniques; vii) self-efficacy for using fruits, vegetables, and seasonings (while cooking); and viii) knowledge of cooking terms and techniques; assessed at baseline, immediately after intervention, and six months after intervention.

#### Secondary outcomes

Body mass index (BMI) of university students as well as their socio demographics and characteristics related to cooking; assessed at baseline, immediately after intervention, and six months after intervention.

### Survey instrument

The evaluation instrument of cooking skills and healthy eating employed in the present study was developed for the CWC program and validated by Michaud [63]. This questionnaire was originally applied in a written form to parents, caregivers [40], and cooks [41]. An online form was given to university students [32]. The NCK instrument was self-administered in online form with use of tablet computers. The use of tablet computers allowed for time optimization and facilitated the survey self-completion by students during the classes. The instrument was cross-culturally adapted to Brazil, according to the following procedures: 1) translation (two independent translations); 2) synthesis of translations (discussion among two translators and one researcher); 3) back-translations (two independent translations compared with the original questionnaire, followed by a discussion among dietitians); 4) expert committee (consensus workshop with experts and university students); 5) synthesis of the final Brazilian Portuguese version; and 6) pre-test (self-administered online questionnaire by 48 university students) [64, 65]. Original and translated questionnaires were compared for conceptual, item, semantic (idiomatic and experiential), and operational equivalencies [66].

The questionnaire items were distributed within eight measures about cooking skills and healthy eating, and a group of items about personal, cooking and demographic characteristics. The process of cross-culturally adaptation and validation of the instrument to Brazil is ongoing and the first paper was published in a scientific journal [67].

Participants were asked to report their demographics and personal characteristics including: age, gender, undergraduate course, type of university admission, parental education level, ethnicity, ascendance, if they have children <16 years old, as well as with whom they live. Cooking characteristics such as daily time available to cook, equipment and utensils available at home, self-reported cooking knowledge, source of cooking experience and lunch or dinner location were also collected to characterize the population of the study. Height and weight were self-reported to enable the calculation of BMI. Table 4 provides a description of each evaluation measure listing instrument or process used and type of data collected by each measure.

**Table 4 Tab4:** Evaluation measures for university students participating in the Nutrition and Culinary in the Kitchen program^a^

Target measurement	Instrument/Process	Description
Demographic characteristics	Student self-report	Birthdate, gender, ethnicity, ascendance, parental education level; composed of six items^b^.
Personal characteristics	Student self-report	Undergraduate course, type of university admission, if they have children <16 years old, with whom they live; composed of four items^b^.
Cooking characteristics	Student self-report	Daily time available to cook, equipment and utensils available at home (39 items), self-reported cooking knowledge, source of cooking experience; and lunch or dinner location; composed of six items^b^.
Height and weight	Student self-report	Student self-report as part of the online survey to enable the calculation of BMI^b^.
Accessibility and Availability of Fruits and Vegetables Index (AAFV)	Cooking skills and health eating questionnaire	Availability of fruits and vegetables over the previous week; composed of eight items with yes/no questions, scored as 1 or 2, respectively^b^.
Cooking Attitude (CA)	Cooking skills and health eating questionnaire	How respondents felt about cooking; composed of seven items with 5-point Likert scale responses (from “strongly disagree” to “strongly agree”) ^b^.
Cooking Behavior at home (CBH)	Cooking skills and healthy eating questionnaire	Frequency of common cooking activities at home; composed of six items with 5-point Likert scale responses (“not at all”, “1 to 2 times a month”, “once a week”, “several times a week”, and “about every day”)^b^.
Cooking Behavior away from home (CBAH)	Cooking skills and healthy eating questionnaire	Frequency of common cooking activities away from home; composed of five items with 5-point Likert scale responses (“not at all”, “1 to 2 times a month”, “once a week”, “several times a week”, and “about every day”)^b^.
Produce Consumption Self-Efficacy (SEPC)	Cooking skills and healthy eating questionnaire	Degree of confidence in meeting the government’s recommendations for the consumption of fruits and vegetables; composed of three items with 5-point Likert scale responses (from “not confident at all” to “extremely confident”)^b^.
Self-Efficacy for Using Basic Cooking Techniques (SECT)	Cooking skills and healthy eating questionnaire	Degree of confidence in performing basic cooking techniques; composed of 18 items with 5-point Likert scale responses (from “not confident at all” to “extremely confident”) ^b^.
Self-Efficacy for Using Fruits, Vegetables, and Seasonings (while cooking) (SEFV)	Cooking skills and healthy eating questionnaire	Degree of confidence in using fruits and vegetables when cooking; composed of nine items with 5-point Likert scale responses (from “not confident at all” to “extremely confident”) ^b^.
Knowledge of Cooking Terms and Techniques (CCT)	Cooking skills and health eating questionnaire	Level of cooking knowledge; composed of eight items with multiple choice answers (correct answer scored as 1 point) ^b^

^a^Measures will be collected at baseline (week 1), immediately post intervention (week 6) and 6 months after the end of intervention (follow-up)

^b^Student self-report in the online survey

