## Methods/design

### Study design

This study used a randomized controlled trial design with six months of follow-up (with repeated measures) to test a community-based cooking skills program to improve cooking and healthy eating behaviors in university students. The study started in 2015 with follow-up studies planned for 2016 and 2017.

The intervention program occurred over a two-month period, one day a week for eight weeks, with two weeks having no intervention topics (due to holiday schedule). The intervention group (IG) data was analyzed at three-time points: (1) on the week prior to the program’s beginning (T1); (2) on the completion of the eight-weeks program (T2); and (3) after six months, on the intervention follow-up period (T3). The control group (CG) comprised participants from the wait-list group who were waiting for 12 months to participate in the study as they continued with their usual practices. Data from this group was analyzed at the same three-time points before they began participation in the program and subsequent comparison with the IG data. After that, the CG will be invited to take part of the NCK program in order to be able to receive the program benefits. Once the study is ongoing, the control group will be invited to participate in the NCK program at the next stage of the study. Thus, the impacts of the intervention program will be evaluated immediately following the post intervention (T2) and the sustained effect, six months after the program (T3) [34, 35] for both groups (CG & IG).

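### As written, the T2 survey setting differs by arm (last cooking class versus e-mailed link) and the intervention group changes mode at T3, so T2 contrasts and changes to T3 may carry a mode effect.

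*Protocol article*

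**What the plan says.** The Survey instrument section states: "The NCK instrument was self-administered in online form with use of tablet computers". It adds that the tablets saved time and "facilitated the survey self-completion by students during the classes". It names no arm or time point.

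Table 3 (Intervention stages) sets out the schedule:

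- **Meeting 1**, "Online survey at baseline (T1"): intervention group, Cooking class 1; control group, "E-mail contact with a link to the online survey".
- **Meeting 6**, "Online survey to be completed right after intervention (T2"): intervention group, Cooking class 5; control group, the same e-mailed link.
- **Meeting 7**, T3: intervention group, "E-mail contact to answer the survey online"; control group, the e-mailed link again.

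The footnote to Table 4 puts baseline in week 1 and the post-intervention survey in week 6, in line with Table 3. The Study design section instead puts the intervention group's T1 "on the week prior to the program’s beginning (T1"), when no class is held.

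On the class setting, Intervention stages says "there were from four to five facilitators and a coordinating teacher for each group of 10 to 12 students". Theoretical perspectives describes spoken positive reinforcement by the dietitian and a closing discussion meant to draw out good experiences.

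The limitations in the Discussion cover general self-report bias, contamination and attrition. They do not mention a difference in survey setting between the arms.

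**The concern.** Seven of the eight primary outcomes are self-ratings or self-reports, and the eighth is an eight-item multiple-choice knowledge test. Such answers can depend on where and among whom they are given. If intervention students answer in the teaching kitchen at the last class while controls answer elsewhere through a link, a T2 difference between arms combines the programme effect with a setting effect.

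The second aim, the sustained effect, is also touched. Between T2 and T3 the intervention group goes from class to e-mail and the control group does not. An apparent fading or persistence of the effect could then partly reflect the change of mode. The planned repeated-measures ANOVA, or Friedman test with Wilcoxon post-hoc tests, works on exactly these within-person changes.

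**Working it through.** **Step 1. Setting by arm and time, as the article reads.**

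| | Intervention | Control |
|---|---|---|
| T1 | class 1 (Tables 3 and 4), or the week before the programme (Study design) | e-mailed link |
| T2 | class 5 (Table 3, with Survey instrument) | e-mailed link |
| T3 | e-mail | e-mailed link |

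The T2 row has no conflicting passage. The T1 row does.

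**Step 2. Where a mode effect enters.** Let m1 and m2 be the average shifts in an intervention student's score from answering in class rather than by e-mail at T1 and T2. At T3 the shift is 0, and for controls it is 0 throughout. The bias in each between-group contrast is then:

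- T2 levels: m2
- T1–T2 change: m2 − m1
- T2–T3 change: 0 − m2 = −m2
- T1–T3 change: 0 − m1 = −m1
- T3 levels: 0

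**Step 3. The possible cases.**

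| Case | T1–T2 change | T2–T3 change | T1–T3 change |
|---|---|---|---|
| T1 in class, constant effect (m1 = m2 = m) | 0 | −m | −m |
| T1 in class, effect differs by time | m2 − m1 | −m2 | −m1 |
| T1 not in class, taken as e-mail like the controls (m1 = 0) | m2 | −m2 | 0 |

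Only the first case protects the T1–T2 change. Constancy is doubtful: at class 1 the students have just met the staff, and by class 5 they have had weeks of reinforcement. No case protects T2 levels or the T2–T3 change. T3 levels are free of a mode difference in every case.

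**Step 4. Scale, by assumption only.** The article gives neither a mode effect nor an SD. For the knowledge score, an SD can be back-solved from the sample size. Reading 28 as per group, with 1.5 points, 80% power and two-sided 5%, n = 2(1.96 + 0.842)² SD²/1.5² gives 28 at SD = 2.0. Then 28/(1 − 0.30) = 40, the stated group size. The SD of 2.0 is therefore an assumption, and it applies to knowledge alone.

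Suppose there is no programme effect, 40 students per group, and a T2 comparison of levels. SE = 2.0 × √(2/40) = 0.447, and the rejection rate is 1 − Φ(1.96 − m2/SE) + Φ(−1.96 − m2/SE).

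| Assumed shift m2 (points) | Share of the 1.5-point target | Rejection rate at nominal 5% |
|---|---|---|
| 0.25 | 17% | 8.6% |
| 0.5 | 33% | 20.1% |
| 0.75 | 50% | 38.9% |
| 1.0 | 67% | 60.9% |

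This shows how sensitive a trial of this size is to a shift. It does not estimate the shift.

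**Step 5. Direction.** Answering among the teaching staff could raise self-ratings in the intervention group. Controls answering alone could look up knowledge items, which would shrink the knowledge difference. Neither is documented, and the two point in opposite directions.

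**The case against.** The strongest reply is that in-class completion at T2 is inferred. The intervention column of Table 3 lists the activity at each meeting and not the survey mode; the tablet sentence names no arm or visit; and a separate validation survey was run in the same student population, so the classes mentioned there might not be the cooking classes. This has some force. Even so, Table 3 alone ties the intervention group's T2 survey to class 5, and it lists e-mail contact for that group only at T3. In-class T2 is the natural reading.

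A reader might go further in several ways that the article does not support:

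- **That T1 was certainly in class.** Study design says otherwise.
- **That the T2 bias is beyond any analysis.** If T1 was also in class and the effect is constant, it cancels in the T1–T2 change, and the outcomes are framed as changes.
- **That the intervention group was supervised while answering.** Staff presence in class is stated; supervision of the survey is not.
- **That students who miss class 5 also miss T2.** Nothing says they are not sent the survey, and the Discussion describes message reminders and recording of attrition.
- **That the bias is a known fraction of the planned effect on most scales.** No setting effect is given, and only the knowledge outcome was sized.
- **That T3 is clean in every form.** It is clean of mode only as a comparison of levels.

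It is also fair that both arms complete the same online instrument, that general self-report bias is disclosed, and that much of the collection may be over: the study began in 2015, follow-up was planned for 2016 and 2017, and the article appeared in December 2017. The analyses are still described in the future tense, so analysis and reporting can be adjusted.

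**Conclusion.** The point holds for T2 and for the mode switch at T3. As written, survey setting differs by arm at T2 for all eight self-completed primary outcomes, and the limitations do not say so. The T2 difference in levels and the T2–T3 change are exposed to a mode effect. The T1–T2 change is exposed unless T1 was also in class and the effect was constant. The T1–T3 change is exposed if T1 was in class. Which of these applies at T1 cannot be settled until Study design, Table 3 and the Table 4 footnote are reconciled.

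Size and direction cannot be estimated from the article and may differ by scale. The conclusion rests on reading Table 3 and the tablet sentence together as in-class completion at class 5. It calls for a cheap improvement and does not show that the trial's results would be wrong.

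**What to change.** 1. Reconcile the T1 timing across Study design, Table 3 and the Table 4 footnote, and state the mode of completion for each arm at T1, T2 and T3.
2. For any remaining or further data collection, send both arms the same e-mailed link on the same dates at all three time points, to be completed outside class with the same reminders. Include intervention students who miss class 5.
3. For data already collected, record the mode and date of each completed survey. Report the T3 between-group difference in levels, where both arms used e-mail, alongside the T2 result. If T1 was in class, show that T3 difference without baseline adjustment, since adjusting with slope b would bring back a bias of −b·m1.
4. Add to the limitations that mode may affect the T2 comparison and the T2–T3 change, and also the T1–T3 change if T1 was in class.

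The cost is one operational instruction, one recorded field and a few sentences. The downsides are a possibly lower intervention-group response than in class and, for an unadjusted T3 comparison, the loss of any precision that the baseline would add. The T2 result stays in the report, since the immediate effect is one of the two stated aims.

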### Statistical analysis

Descriptive analysis of the sociodemographic variables and of the student characteristics at baseline will be conducted with measures as mean and standard deviation for symmetrical numeric variables, or median and interquartile interval for asymmetrical numeric variables. For categorical variables, the description involves the prevalence of data (absolute and relative frequencies).

T-test (for parametric data) or Mann-Whitney test (for non-parametric data) will be run to verify the differences intragroup, among control groups and intervention for the pre-intervention condition (baseline) with continuous variables. For categorical and parametric variables, chi-square test or chi-square fisher’s exact test will be used.

Intervention’s effect will be evaluated by means of the analysis on the changes in cooking skills and healthy eating survey. Issues related to the scales evaluated by the instrument (in T1, T2, and T3) will be analyzed to verify data normality. Subsequently, ANOVA for repeated measures (for parametric data) or Friedman (for non-parametric data) followed by Wilcoxon signed rank test (post-hoc test) will be employed.

Data collected through the online survey will be transferred to Microsoft Office Excel® and exported to Stata® version 13.0 (Statacorp, College Station, TX, USA). Statistical analysis will be run on Stata® and a significance level of 5% will be adopted, considering *p* < 0.05.

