### Sample size calculation

Sample size calculation for the intervention aimed at detecting changes in the average values of the outcome related to cooking skills knowledge [32]. Considering a difference of 1.5 points in average [32], with study power of 80%, an error rate of 5% and a 95% level of confidence, a sampling plan of 28 students was estimated. Including a random loss of 20% and 10% for possible confounding factors, a minimum sample of 40 students was suggested to be investigated in each group (intervention & control), involving a total sample of 80 participants. Sample size calculation was carried out with the statistical program Open Epi version 3.03 (Open Source Epidemiologic Statistics for Public Health, Atlanta, GA, USA).

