### Randomization

Participants who were accepted to take part in the study were randomly assigned to groups (IG & CG), to ensure homogenization and a similar number of participants in each of the groups. Participants’ random order to each group was determined with the help of the online software *Research Randomizer* (https://www.randomizer.org/). Students were not informed about which group they were assigned since all students would have the opportunity to participate in the NCK program in time. Control group participants were informed that they would take part in the intervention program after answering online surveys in three distinct moments (T1, T2, and T3), characterizing them as part of the wait-list control group.

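### The sample is enlarged by 10% for confounding, but no named analysis adjusts for any characteristic, and the baseline significance tests cannot do that job

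*Protocol article*

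**What the plan says.** Four places in the protocol article bear on imbalance between the groups.

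- **Sample size calculation.** The text says "a sampling plan of 28 students was estimated", and then "Including a random loss of 20% and 10% for possible confounding factors" arrives at 40 per group. The Abstract repeats the two allowances.
- **Randomization.** A random order from online software is used "to ensure homogenization and a similar number of participants in each of the groups". No stratification factor is named.
- **Statistical analysis, baseline.** T-tests or Mann-Whitney tests "will be run to verify the differences intragroup, among control groups and intervention for the pre-intervention condition (baseline) with continuous variables", with chi-square or Fisher tests for categorical variables. Nothing is said to follow from a significant or a non-significant result.
- **Statistical analysis, effect.** Changes in the survey scales over T1, T2 and T3 are analysed by repeated-measures ANOVA, or by Friedman followed by Wilcoxon signed rank tests. No covariate, regression or stratified analysis is named.

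Two further statements matter. The Abstract announces that relations with personal characteristics will be explored, without a method. The Discussion says that randomisation is the only means of removing confounding.

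**The concern.** These statements do not fit together. The sample is sized partly for confounding, the analysis contains nothing that deals with it, and the Discussion says that randomisation already has. The baseline tests look like the intended safeguard, but they are a poor one. In a randomised trial any baseline difference is due to chance, so the p-value tests a hypothesis already known to be true. With about 40 per arm, a non-significant result does not show that the groups are alike.

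At stake is whether a chance imbalance in, say, gender, prior cooking knowledge or time to cook goes unnoticed and unadjusted, and whether prognostic information already collected at T1 is left unused.

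**Working it through.** **1. The plan's own figure.** Inputs: 28 before allowances, 20% loss, 10% confounding (Sample size calculation). I read 28 as per group, the reading that leads to 40 per group.
- Both allowances: 28/(1 − 0.30) = 40. The stated figure reproduces.
- Loss only: 28/(1 − 0.20) = 35.
- The confounding allowance is therefore 5 per group, 10 in total.

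**2. What the five students buy.** No SD is given. For a two-sided 5% test with 80% power and a 1.5-point difference, the implied SD is 1.5 × √(28/2)/(1.96 + 0.84) ≈ 2.0. After a 20% loss, 40 leaves 32 and 35 leaves 28.
- Normal approximation, Φ(1.5/(2.0 × √(2/n)) − 1.96): n = 28 gives Φ(0.85) = 0.80; n = 32 gives Φ(1.04) = 0.85.
- With the t distribution the figures are 0.79 and 0.84.

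The allowance buys about 5 points of power. It also narrows chance imbalance slightly: the SD of a standardised baseline difference is √(2/28) = 0.267 against √(2/32) = 0.250.

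**3. What the baseline tests can see.** 41 per arm (Sample recruitment and selection).
- Smallest flagged difference: t(0.975; 80 df) × √(2/41) = 1.99 × 0.221 = 0.44 SD.
- Chance that one continuous variable differs by more than 0.3 SD: 17%.
- Chance that a 50% binary factor differs by 15 percentage points or more: 18% (hypergeometric, 82 students, 41 per arm).
- About 25 variables (8 scales, BMI and the 6 + 4 + 6 characteristics in Table 4): 25 × 0.05 = 1.25 chance flags expected, and 1 − 0.95^25 = 72% for at least one if independent.

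**4. Effect on the error rate.** A simulation of 40,000 trials compared one outcome at one time point, with 32 per group and a covariate correlated r with the outcome (r assumed).

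| r | Overall type I error | Given imbalance > 0.25 SD | Given imbalance > 0.25 SD that the test misses |
|---|---|---|---|
| 0.3 | 0.050 | 0.067 | 0.060 |
| 0.5 | 0.050 | 0.091 | 0.075 |
| 0.7 | 0.050 | 0.125 | 0.087 |

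An imbalance above 0.25 SD occurs in about 31% of randomisations. These figures are for outcome levels. For changes they are smaller wherever the covariate relates to T1 and follow-up alike (step 5).

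**5. Why analysing change limits the effect.** For a change from T1, the shift from an imbalance is imbalance × (r at T2 − r at T1) × SD. Take an imbalance of 0.43 SD, just below the flagging limit:
- r = 0.5 at both times: 0.43 × 0 × 2.0 = 0.
- r = 0.5 at T1 and 0.3 at T2: 0.43 × 0.2 × 2.0 = 0.17 points in absolute size.

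**6. What adjustment would gain.** With residual SD 2.0 × √(1 − r²) and 32 completers per group, power by the normal approximation is 0.88, 0.93 and 0.99 at r = 0.3, 0.5 and 0.7, against 0.85 with no baseline information. Against an analysis of change the comparison differs: adjusting for the T1 score leaves (1 − r²)/(2(1 − r)) = (1 + r)/2 of the variance of a change score, that is 65%, 75% and 85%, where r is the T1 to follow-up correlation.

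**The case against.** The strongest reply is that nothing here is invalid. Unadjusted analysis of a randomised trial is legitimate, the protocol says it relies on randomisation, and overall type I error is 5% at every correlation tried. That stands. So does the remark that the baseline tests select no analysis, so their chance flags distort no result, and that a separate analysis plan, not shown, may name covariates. What remains is the mismatch in the published text: a stated allowance for confounding beside a list of methods that has no place for it.

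Three stronger readings are tempting, and the document supports none of them.
- **That the 10% is wasted.** It is not; it adds about 5 points of power.
- **That an imbalance passes whole into the treatment comparison.** On outcome levels, 0.43 SD with r of 0.3 to 0.5 would shift the knowledge contrast by 0.26 to 0.43 points, or 17% to 29% of the 1.5-point target. But the plan analyses changes, so the stable part of a characteristic cancels (step 5). The 0.43 SD is also a near-worst case: the average unflagged imbalance is about 0.16 SD.
- **That sizeable imbalance is to be expected in any given variable.** The chances in step 3 are 17% and 18%.

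**Conclusion.** The point holds as a mismatch between the Sample size calculation and the Statistical analysis sections, and as a missed gain in precision. It does not show bias. The allowance is labelled as protection against confounding, which a larger sample does not give. The baseline tests neither correct imbalance nor detect it below about 0.44 SD, and nothing follows from them. The cost is some precision in every primary comparison and an error rate above 5% in trials that happen to be imbalanced on a prognostic factor. Both are modest, because T1 is already part of the analysis.

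The sizes rest on a two-sided 5% test, 28 read as per group, the implied SD of 2.0, and assumed correlations of 0.3 to 0.7. None of the correlations comes from the document.

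**What to change.** 1. **Statistical analysis.** For each primary scale, estimate the between-group difference at T2 and at T3 in a model adjusted for the T1 score and a short prespecified set already collected at T1, for example gender, self-reported cooking knowledge and daily time available to cook. Apply it whatever imbalance is observed. Enter the covariates so that they act on the T2 and T3 contrasts, by ANCOVA or with covariate-by-time terms. A time-constant covariate added to repeated-measures ANOVA only as a main effect leaves the group-by-time effect unchanged.
2. **Baseline table.** Keep the descriptive summary already planned, shown by group, and drop the p-values.
3. **Sample size calculation.** Describe the 10% as a margin for power. Recruitment has already reached 82, so no number needs to change.

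The cost is wording and a few model parameters, with no new data and no extra participants. Only the first item can alter an estimate; the other two make the text consistent.
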